***Eligibility criteria and randomization***

Forty communities were assigned into 8 strata on the basis of the prevalence of diarrhea in under-five children, economic status of the community, and the proportion of mothers who delivered their youngest child by a skilled birth attendant based on the results of the first-round survey. To evaluate the socioeconomic status of a community, we used the proportion of households with wattle and daub houses as representatives of the lowest economic level. We ensured that an equal number of communities within all 8 strata were randomly allocated into the intervention and control arms, with each arm including 20 communities. Microsoft Excel version 15.22 was used for randomization. We ensured comparability in the main outcomes between the intervention and control arms by strictly applying randomization. After conducting the first-round survey, we classified the clusters into strata by primary endpoint and socioeconomic status. In doing so, we were able to ensure a high comparability and therefore were able to avoid selection bias. Control communities are allocated by randomization among the target communities. We found control and intervention communities well balanced in terms of caregivers’ demographic and socioeconomic status, and child demographic status and several key variables related to primary outcomes of the intervention (Table 2).

Figure 2. Flow diagram of the trial.

| [figure not shown] |
| --- |

Table 2. Results of the first-round survey in the intervention and control arms.

| **Variables** | | **Intervention** | | **Control** | |
| --- | --- | --- | --- | --- | --- |
|  |  | N | % or  mean (SD^2^) | N | % or  mean (SD) |
| Caregiver's age (years) | | 999 | 29.00(7.16) | 957 | 28.86(6.78) |
| Religion of respondent | Christian | 614 | 61.50% | 599 | 62.60% |
|  | Traditionalist | 280 | 28.00% | 256 | 26.80% |
| Education level of respondent | Graduated basic school | 188 | 23.6% | 165 | 22.5% |
|  | Dropped out of basic school | 455 | 57.2% | 406 | 55.3% |
|  | Graduated secondary school | 19 | 2.4% | 24 | 3.3% |
| Possession of NHIS^1^ Card | Have a valid card | 332 | 33.2% | 328 | 34.3% |
| Age of the youngest child under-5 child (In months) | | 989 | 22.97 (15.95) | 946 | 21.97 (15.94) |
| Youngest child’s sex | Male | 505 | 50.6% | 483 | 50.5% |
| Main source of drinking water for the last-born child | Hand-dug well | 268 | 26.8% | 248 | 25.9% |
|  | Sachet water | 202 | 20.2% | 223 | 23.3% |

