***Data analysis***

Intention-to-treat analysis will be conducted to explore the effect of CHV activation on childhood infectious disease of under-five children. For diarrheal prevalence as a dependent variable, water quantity and quality, hygiene behavior of caregivers, presence of improved latrines, characteristics of the enrolled child such as age and sex, household income, and caregiver’s education level will be controlled for in quantifying the net effect of CHVs. For malaria prevalence as a dependent variable, the enrolled child’s characteristics, household income, and caregivers’ education level will be controlled. Environmental risk factors such as seasonality and altitude are also considered to be independent variables for malaria prevalence. However, the intervention and control arms in our study site present no difference in those factors so there will be no control for environmental factors. When quantifying the net effect of CHVs on child malaria prevalence, insecticide-treated bed net utilization will not be controlled since it is considered an intermediate factor between intervention and disease outcome. Generalized estimating equations will be used for investigation at the cluster level. The random effects model will be used, taking account of between-cluster variation by assuming that there are cluster-level effects. Per-protocol analysis will be performed to obtain additional background information if the overall percentage of CHVs activated does not reach 80%. Multi-level analysis will also be conducted to explore whether the effects of CHVs on child diarrheal and malaria prevalence vary by community depending on a community’s overall coverage of activated CHVs.

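### The planned adjustment sets leave out the eight randomisation strata, and GEE and a random-effects model are both specified with neither named as primary

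*Protocol*

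**What the plan says.** Under Eligibility criteria and randomization, the protocol reports that "Forty communities were assigned into 8 strata on the basis of the prevalence of diarrhea in under-five children, economic status of the community"; the third factor is skilled birth attendance. On the allocation itself it states "We ensured that an equal number of communities within all 8 strata were randomly allocated into the intervention and control arms". The total is 20 communities per arm.

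Under Data analysis it names the variables to be adjusted for. For diarrhoea these are "water quantity and quality, hygiene behavior of caregivers, presence of improved latrines, characteristics of the enrolled child such as age and sex, household income", plus caregiver education. For malaria they are the child's characteristics, household income and caregiver education. The section explains why environmental factors and bed-net use are left out of the malaria model. The strata appear in neither list, and no reason is given.

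On the cluster model the section says "Generalized estimating equations will be used for investigation at the cluster level. The random effects model will be used, taking account of between-cluster variation". Neither model is called primary and neither is tied to a particular endpoint. The multi-level analysis mentioned later has a separate exploratory aim, which is whether the effect varies with a community's coverage by activated volunteers.

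**The concern.** Two things look wrong.

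First, stratified allocation removes between-stratum variation from the true sampling error of the arm difference. An analysis that ignores the strata leaves that variation in the estimated standard error. The error is then overstated to the extent that the strata are prognostic, and the precision that stratification bought is not used. One stratifying factor, community diarrhoea prevalence, is the first-round value of a primary endpoint, so it may well be prognostic. Household income covers the community housing factor only in part. Nothing in either list stands in for community diarrhoea prevalence or skilled delivery.

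Second, for a binary outcome with a logit link, GEE and a random-effects model estimate different quantities, have different standard errors and can give different p-values. With several primary endpoints, there are two candidate results for each. If the second sentence was meant only to describe the GEE, it describes it wrongly, because GEE does not assume cluster-level random effects.

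**Working it through.** **Inputs from the protocol.** 20 clusters per arm; 8 strata; p0 = 0.25; 25% relative reduction, so p1 = 0.1875; coefficient of variation k = 0.16; 950 households per arm (47.5 per cluster, 42.75 after 10% loss); 80% power.

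**Assumptions.** Two-sided alpha of 0.05 (not stated in the protocol); equal cluster sizes of 43; stratum sizes 6, 6, 6, 6, 4, 4, 4, 4 (the average of 40/8 = 5 is odd, so a 1:1 split needs unequal strata); and a range for R², the share of between-cluster variance that the strata explain. The protocol gives no figure for R².

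**The plan's own figure.** The protocol gives no type I error or power for its analysis model. The nearest figure is the sample size:

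c = 1 + 7.849 × [(0.1875 + 0.1523)/n + 0.16² × (0.25² + 0.1875²)] / 0.0625²

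- n = 47.5: c = 20.4, or 19.4 without the added 1. Before loss this agrees with 20 clusters.
- n = 42.75: c = 22.0, or 21.0 without the added 1. The 950 is therefore not reproduced once the 10% loss is applied. That is a separate matter. Here it shows only that power after loss is about 76% to 78%, with little to spare.

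**Why omitting the strata is conservative.** The variance of a cluster proportion is 0.1875/43 + (0.16 × 0.25)² = 0.00436 + 0.00160 = 0.00596. If strata explain R² of the between-cluster part, they account for a share s = R² × 0.00160/0.00596 of the total. The t statistic on 38 df is then too small by a factor of √(1 − s), so type I error is about P(|t38| > 2.024/√(1 − s)).

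| R² | s | Approximation | Simulated (10,000 runs), corrected t, strata ignored |
|---|---|---|---|
| 0 | 0 | 5.0% | 4.9% |
| 0.25 | 6.7% | 4.3% | 4.2% |
| 0.50 | 13.4% | 3.6% | 3.6% |
| 0.75 | 20.1% | 2.9% | 2.9% |

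**With the strata included.** A cluster-level t-test on 40 − 2 − 7 = 31 df has simulated type I error of 4.8% to 5.2% across the same range.

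**Power for the planned effect (5,000 runs, 43 per cluster).** At R² = 0, power is 77.0% without the strata and 76.6% with them. At R² = 0.5 it is 76.8% and 80.6%.

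**If the GEE used an uncorrected sandwich z-test (a conditional case).**

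- Strata ignored, R² = 0, closed form: P(|t38| > 1.96 × √(19/20)) = P(|t38| > 1.910) = 6.4%. Simulated: 6.5%, 5.3%, 4.7% and 3.7% at R² = 0, 0.25, 0.50 and 0.75. Logistic exchangeable GEE (2,000 runs each): 5.6%, 5.2% and 3.4% at R² = 0, 0.3 and 0.6.
- Seven stratum indicators added, closed form: P(|t31| > 1.96 × √(31/40)) = P(|t31| > 1.725) = 9.4%. Simulated: 9.2% to 9.6%. Logistic GEE: 8.2% to 9.2%.

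**The correction itself matters.** The 4.8% to 5.2% above belongs to the cluster-level t-test. In the logistic GEE runs with strata, the Mancl-DeRouen variance with t on 31 df rejected in only 2.4%, 2.5% and 1.9% of runs at R² = 0, 0.3 and 0.6 (means of four batches of 500). That is an over-correction.

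**How far apart the two models are.** On the logit scale the between-cluster SD is about 0.04/0.1875 = 0.213, with variance 0.0455. The usual attenuation factor is 1/√(1 + 0.346 × 0.0455) = 0.992, so the two log odds ratios differ by under 1% at the protocol's own k.

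**The case against.** The strongest reply has three parts.

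- **The test is not shown to be invalid.** A reader might infer that the GEE is uncorrected and that the p-values will miss their nominal size. The protocol supports neither inference. It names no variance estimator, working correlation or reference distribution, and these are commonly left to a statistical analysis plan, which is not at hand. Even on the uncorrected reading, omitted strata (conservative) and the sandwich bias (liberal) pull in opposite directions. The cluster-level runs give about 3.7% to 6.5%, which can land on 5%. The 8% to 10% figure arises only if strata are added without a correction, which the protocol does not propose. This part stands in full.
- **The gain from the strata is small and uncertain.** It is nil if they explain nothing and about 4 points of power if they explain half of the between-cluster variance. No figure in the protocol shows how far they predict fever, the endpoint that was powered. This stands as a limit on size. It does not explain why lists that give reasons for other exclusions leave out the design factors.
- **The two models nearly agree.** The point estimates would be close at k = 0.16. This stands for the estimate, but standard errors and p-values can still differ, and the text ranks neither model.

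**Conclusion.** Two facts hold on the face of the protocol: both covariate lists omit the strata used for allocation, and two cluster models with different estimands are specified without a primary.

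The consequence is modest. Ignoring the strata errs towards caution and gives up some precision, by the amounts shown in the working. These figures rest on a two-sided 5% level, equal clusters of 43, the protocol's k of 0.16, the assumed stratum sizes and the assumed range for the variance explained. The lack of a primary model is mainly an ambiguity about which standard error and p-value count.

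Nothing here shows that the planned p-values must be wrong. The point is a worthwhile, inexpensive correction.

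**What to change.** - Name one primary model and one effect measure for each primary endpoint. Keep the other model as a sensitivity analysis, and reword the random-effects sentence so that it does not read as a description of GEE.
- Include the randomisation strata in the primary model, either as eight levels or as the three underlying factors. If the eight strata are a 2 × 2 × 2 classification, three indicators leave 40 − 2 − 3 = 35 df in place of 31.
- Make the small-sample choice in the same change: a corrected variance with a t reference on cluster-based degrees of freedom (about 31 with eight strata), or a permutation test within strata. Check the chosen combination by simulation at the trial's own layout, since an uncorrected z-test with strata is liberal (about 8% to 10%) and the Mancl-DeRouen variance with t on 31 df was conservative (about 2%).

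The cost is analysis wording and up to seven degrees of freedom, with slightly wider intervals if the strata turn out not to be prognostic (power 76.6% against 77.0% in that case). No change to data collection is needed, because the strata come from the first-round survey.

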**DISCUSSION**

This study seeks to assess the effects of CHVs on the health gains of children under 5 years of age. We thus rigorously applied a randomization process after calculating adequate cluster and household sample sizes.

In this study, we place an emphasis on the preventive role of CHVs in child health. The role of CHVs is to provide education about hand-washing, breastfeeding, the utilization of insecticide-treated nets, ORS treatment and rapid malaria tests, as well as making referrals for sick children to health facilities. We expect the health education using key messages during home visit will facilitate their function for disease prevention. Considering the context of resource-poor settings, the public health implications of the preventive role of CHVs is not trivial.

Previous studies did not describe the nature of CHV training or the availability of further education after the initial course. In this trial, CHVs are trained one week at the start of the project and regular training will be provided on a monthly basis by CHOs and CHNs.

We performed a pre- and post-test right before and after the CHV training. If we found a CHV not achieving a score of 80 out of 100, we retrained him or her. To standardize the regular training, standard operating procedure on the implementation of monthly meetings will be provided to the supervisors of the CHVs and it includes the guidance on the training. The regular training will be conducted based on the topics and messages from the home visit booklet that CHVs were provided with to facilitate their home visit education. Also, the monitoring team, composed of the district health directorate members and the project manager and staff, who oversee the monthly meeting and training activities of all CHVs, will coordinate the content and quality of regular training through active review and discussion.

The intervention is not restricted to health education. According to the operational definition of this trial, the key intervention is to help CHVs perform their duties, which mainly involve visiting at least 20 households each month to deliver key messages and provide basic health services established by the policy such as malaria diagnosis and ORS provision.

Through in-depth discussion with government officials and community leaders during project design, we realized that merely educating CHVs was not sufficient to help them perform their tasks. We thus developed active supervision and support from government officials such as CHPS in close collaboration with DHMT. By employing a phase-in design for the trial, the government made an agreement that CHV activation would be delayed in the control arm during the first phase since it could be carried out during the second phase. In this regard, we believe that contamination will not take place severely.

No monetary subsidies will be provided to CHVs during the trial to strictly comply with the policy of the Ghanaian government, according to which CHVs function as a bridge between community members and CHNs “without affecting the national wage bill,” and rely on the discretion of community members.

One of the strengths of this trial is that a process evaluation will be conducted in parallel with the impact evaluation. Few studies have investigated the impact of CHWs using process indicators. In this study, we will use process indicators at each stage to assess reliability, services delivered, services received, participation, recruitment, retention and quality. A range of data will be collected and analyzed to evaluate each process: the appropriateness of selection of CHVs, the quality of their training, the frequency of their visits to each household every two months, the number of key messages delivered to each household, the number of key messages caregivers can recall, community participation in relation to CHV activities, their retention rate, and changes in preventive and health-seeking behaviors. Implementation of process evaluation will ensure that we explore how the entire health system affects the activation of CHVs in terms of supervision, logistics, incentives, and by what mechanism this occurs. Four rounds of a household survey will be administered to collect data regarding the project process, where we will assess the extent to which CHVs will be supported by the community nurses and the entire health system as a whole.

One of the limitations of this trial is that malaria cases are not being confirmed using laboratory tests. We will measure fever reported by a caregiver as a proxy indicator of malaria prevalence in both arms of the trial. Although RDTs will be used to test for malaria in children with a fever, this will only be the case for households within the intervention arm since the testing will be conducted by CHVs. Despite its seasonal variance, fever, as the primary manifestation of malaria in young children, can be utilized as an indicator of malaria prevalence, although some source has suggested that it must be interpreted with caution [36].

The project team must start recruiting CHVs in control arm during the second phase and also reached an agreement with the local governments to commence CHV activation without any further delay right after the first phase regardless of any pronounced effects on children. If we have to implement CHV activation in the control arm, we cannot maintain two different arms with and without intervention, which means we cannot compare the outcomes of the intervention during this phase. Hence, we ruled out an optimization phase. We thus cannot consider an optimization phase for this trial although we think optimization is important.

Due to the absence of demographic data for the study district, we used estimated population figures for each community derived by the officials of the Ghana Health Service. However, during the baseline survey we found discrepancies between the estimated and actual number of households in communities, and these figures were adjusted during the sampling process in some communities. Although a pre-survey listing the households in each community is recommended to enhance the accuracy of household sampling, budgetary constraints prevented us from carrying out such a survey.

CHWs are expected to offer quality health services to the population at a reduced cost. To that end, CHWs have been often required to perform extensive duties, such as health extension workers in Ethiopia or CHWs in Kenya.^11, 37^ However, the quality of care may be harmed when CHWs are overloaded or given complicated tasks with only limited training.^37^ CHVs in Ghana are voluntary CHWs who are given a short period of training and a limited range of responsibilities, focusing on promotional and preventive health services. Therefore, this study exploring the effects of CHVs on child health will provide useful information regarding the adoption of voluntary CHW programs in sub-Saharan Africa.

As incased attention has been paid to the role of CHWs in community health systems in low-income settings, the roles, incentives, and training program involved have become increasingly diversified, which hinders a clear assessment of the effects of different types of CHW programs.^10^ This study will be a step forward in specifically testing the effectiveness of voluntary CHW cadres.

**Declarations**

**Acknowledgements** The authors thank participating community members, and Ghana Health Service.

**Funding** This project is funded by the Korea International Cooperation Agency (KOICA). The content of this publication is the responsibility of the authors and do not reflect the views of KOICA.

**Availability of data and materials** Study materials and data will be held by the KOICA. All study materials and data-sets are available on request from the corresponding author.

**Consent for publication** Not applicable.

**Ethics approval and consent to participate** Ethical approval to conduct the study has been obtained from the Ghana Health Service Ethics Review Committee (reference number GHS-ERC:07/01/15). The trial is currently being conducted according to good research practice and we obtained written informed consent from the participants by informing participants about the study and by asking for their informed consent to participate.

**Competing interests:** The authors declare that they have no competing interests. [name] declared that he had no competing interests in a written form.

**Data sharing statement:** In addition to the paper and the protocol, the informed consent documents and all the report forms are available on request.

**Contributors:** [name], [name], [name] and [name] conceived the study, and [name] and [name] led the study design. [name] and [name] provided expertise in the trial of the implementation of community health volunteers. [name], [name], [name], [name] and [name] participated in the design of the study and the implementation of the trial, and edited the manuscript. [name], [name], [name] and [name] drafted the manuscript. [name] provided expertise on cluster-randomized trials. All authors read and approved the final manuscript.

